#### EXPERIMENTAL DESIGN

The design is a smoking replacement trial, in which we will compare changes in upper airway ion transport and inflammation in smokers who switch to EC vaping versus subjects that continue to smoke tobacco cigarettes. In addition, we will use the trial design to evaluate the feasibility of using the EC as a means to quit tobacco use.

*Study population/recruitment.* We plan to study the effects of continuous EC vaping (3 months) in 30 active smokers that successfully switch to ECs (a smoking replacement trial). For this, we plan to enroll approximately 200 active smokers (screening phase), expecting that only one fourth will be able to stay abstinent from tobacco and keep exclusively vaping the ECs after a month. The 30 subjects who can remain tobacco-smoke free for the initial 4 weeks will undergo the study procedures, as >90% of them are likely to remain on ECs for the next few months (49) (as opposed to what is observed in a smoking cessation trial (48)). Twenty additional smokers who wish to continue to smoke will be enrolled as well for the comparator group. Subjects that actively smoke and have a history of at least 5 pack-years will be invited to participate. Exclusion criteria include HIV, marijuana use, COPD, asthma and other concomitant inflammatory pulmonary disorders, subjects with known pulmonary diseases including malignancies, subjects with prior thoracic surgery and subjects that used oral corticosteroids or antibiotics within the prior 3 months, subjects with allergies to study medications and subjects incapable of providing informed consent. Subjects must be in stable condition.

Subjects will be enrolled primarily in the pulmonary function test laboratory, pulmonary and primary care clinics. We will place IRB-approved advertisements in clinics if necessary. Recruitment will occur over a course of 5 years.

The study will have 4 Phases: transition, stability, weaning and surveillance.

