*Phase I: transition from tobacco use to EC (4 weeks):* After signing informed consent, all subjects entering the screening phase will have pulmonary function testing (PFT) if none available in the prior month and we will record basic demographic and social history. After obtaining an initial blood sample (plasma), we will provide and instruct the subjects how to use the EC (eVic®). The nicotine content of the “e-liquid” provided (a PG:VG mix 50:50) will match the number of cigarettes smoked a day and will vary from subject to subject (see below for calculation). We will use the 12 mg/ml concentration e-liquid. During this “transition phase” period we will assess their success of abstaining from smoking tobacco. To monitor abstinence to tobacco smoking, subjects will be seen in person weekly for measurements of exhaled CO (ExCO), and venous COHb. ExCO > 6 ppm (50) or venous COHb >1.6% (51) will be considered the result of tobacco cigarette use. In addition, we will measure urinary marijuana with a qualitative test and if positive we will exclude the subject from the study. During those visits we will assess vaping compliance by downloading the vaping history of the EC using the myVapors® software, available from the EC manufacturer and will collect data regarding potential side effects. Subjects will be encouraged to transition solely to EC within the first 4 weeks. Blood draws for biomarker assessment will be performed in each visit of this phase.

*Phase II: Stability on EC (12 weeks):* In this phase, subjects will remain on EC use for three months. In this phase, all subjects will continue to use ECs at a stable nicotine concentration for additional 12 weeks. Tobacco use abstinence will be monitored every week as in the transition phase as detailed in Table 1. High ExCO levels will be confirmed with venous COHb if necessary. Oral washes and nasal lavages will be done at the beginning and the end of this phase.

Smoker controls: 20 tobacco smokers will be directly enrolled in the “stability” phase, where they will continue to use their regular tobacco for 3 months. They will undergo nasal samplings and NPDs before and after, with monthly blood collections. After this phase, these control subjects may be re-enrolled in the study to start in the transition phase with EC.

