### 1. Risks to the Subjects

A) Human Subjects Involvement and Characteristics: We will enroll active smokers older than 18 years, who actively smoke and have a smoking history of at least 5 pack-years. These subjects should not be currently using ECs but should be willing to replace tobacco cigarettes to ECs. All subjects will undergo lung function testing to exclude chronic obstructive pulmonary disease, as this condition may not only increase the risk of procedures but also impose additional inflammatory confounders. Exclusion criteria include the presence of airflow obstruction ( $FEV_1/FVC < LLN$ ), other concomitant inflammatory pulmonary disorders (i.e asthma), subjects with known pulmonary malignancies, subjects with prior thoracic surgery and subjects that used oral corticosteroids or antibiotics within the prior 3 months, subjects with allergies to study medications and subjects incapable of providing informed consent. Subjects must be in stable condition. Considering that about 75% will not be able to stay abstinent from tobacco cigarette smoking, we expect to screen 120 subjects, who meet these criteria, to be able to have 30 subjects who will complete all study procedures 3 months apart. In addition, we will enroll 20 active smokers unwilling to quit tobacco smoking but willing to undergo the study procedures using the same exclusion criteria. Since these trials will be performed at the Miami Veterans Affairs (VA) Medical Center, we expect that subjects will be >90% men, 20% Hispanic and 25% African American.

B) Sources of Materials: The following are the procedures that will be performed:

Collection of nasal lavage fluid: Nasal lavage fluid will be used to measure changes in epithelial inflammatory cytokines. The lavage will be performed using saline pre-warmed to 37°C. The subject will keep the head bent forward with the face held horizontally, while the left nasal cavity is filled with saline, using a 10 ml syringe connected to the nostril via a short tube and a nasal olive. After 5 minutes approximately 5 ml of the saline is recovered by aspiration. The samples will be centrifuged to remove cellular debris and aliquots of the supernatants stored at -20°C in microcentrifuge tubes until analysis.

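### Switchers are selected by willingness and a 4-week run-in that about 75% are expected to fail, controls by unwillingness to quit, and the only stated adjustment cannot correct for that selection

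*Protocol*

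**What the plan says.** All references are to the protocol.

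- **Comparison.** Experimental Design sets out a comparison of changes in upper airway ion transport and inflammation between smokers who switch and smokers who continue. No randomisation is described.
- **EC group.** Human Subjects, 1. Risks to the Subjects, A) requires of EC candidates: "These subjects should not be currently using ECs but should be willing to replace tobacco cigarettes to ECs". Study population/recruitment plans the run-in "expecting that only one fourth will be able to stay abstinent from tobacco and keep exclusively vaping the ECs after a month". Only subjects tobacco-free for those 4 weeks go on to NPD and nasal sampling. Under Expected Results, subjects later suspected of smoking are excluded, and recruitment continues until 30 complete.
- **Controls.** Risks to the Subjects, A) says "we will enroll 20 active smokers unwilling to quit tobacco smoking but willing to undergo the study procedures using the same exclusion criteria". Under Smoker controls, "20 tobacco smokers will be directly enrolled in the" stability phase, with NPD and nasal sampling before and after 3 months of usual tobacco use and monthly blood collections.
- **Timing.** Table 1 puts the first NPD at V5 and the second at V16. Expected Results confirms that switchers have already used ECs for 4 weeks at the first NPD.
- **Adjustment.** The Statistical Analysis paragraph names two items: nicotine exposure (urinary nicotine and cotinine) and EC puffs per day.
- **Eligibility.** Study population/recruitment states: "Exclusion criteria include HIV, marijuana use, COPD, asthma". The list in Risks to the Subjects, A), which controls are to share, contains neither HIV nor marijuana. Phase I adds that "we will measure urinary marijuana with a qualitative test and if positive we will exclude the subject from the study".

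**The concern.** The protocol wants to learn whether ECs are more or less harmful than continued smoking, and it rests this on the smoker comparator. The two groups are formed by opposite rules. One consists of willing smokers who have shown that they can stop. The other consists of smokers who do not want to stop and were never tested. Ability to stop plausibly goes with lower smoking intensity and dependence, and these may also bear on how smoke-related inflammation and ion transport develop. A between-group difference could then reflect who can quit rather than what is inhaled.

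A named adjustment might be expected to deal with this, but the one stated concerns exposure after the switch. The eligibility text adds a smaller problem. It can be read so that some exclusions bind the EC group but not the controls.

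**Working it through.** **1. Strength of the filter.** Inputs: 30 EC subjects wanted and about 75% expected to fail the run-in (Risks to the Subjects, A).

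- Starters needed = 30 / (1 − 0.75) = 120. This reproduces the protocol's figure: "Considering that about 75% will not be able to stay abstinent from tobacco cigarette smoking, we expect to screen 120 subjects".
- The Planned enrollment tables agree. Potential EC users: 20 + 16 + 28 + 32 + 24 = 120. EC first NPD: 5 + 4 + 7 + 8 + 6 = 30. Controls: 6 + 4 + 4 + 2 + 4 = 20.
- Study population/recruitment gives another number: "we plan to enroll approximately 200 active smokers (screening phase". At 25% that yields 200 × 0.25 = 50 subjects, not 30. If only 30 come from 200, the pass rate is 30 / 200 = 15%.

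On the protocol's own figures the run-in therefore removes between 75% and 85% of EC starters. Controls pass through no such filter.

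**2. What a comparison of changes removes.** Write a subject's measurement as a personal level, plus a personal drift over the stability phase, plus any product effect. Subtracting the first NPD from the second cancels the level. The difference between groups in mean change is then:

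(product effect accruing between V5 and V16) + (mean drift in switchers − mean drift in controls).

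The second bracket is zero only if the selected switchers and the unwilling controls would have followed the same course under the same exposure. Nothing in recruitment secures that.

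**3. Baseline.** V5 follows the 4-week transition. The EC group has no NPD before the switch, so its baseline already mixes selection with early effects of stopping tobacco and starting ECs. The controls' first NPD is taken during usual smoking.

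**4. What the stated adjustment can do.**

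- EC puffs per day exist only after the switch. They have no counterpart in a subject who only smokes, so the covariate largely duplicates group membership.
- Nicotine exposure is given without a time point. Paired with puffs per day, it reads as exposure during the study. The protocol matches each switcher's nicotine dose to prior smoking and then lets subjects adjust their use, so this value need not reflect smoking intensity before the switch.
- Expected Results anticipates that nicotine itself affects NPD. Adjusting for on-study nicotine may therefore also remove part of the effect under study.

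Neither item describes the subjects before they were sorted into groups.

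**5. Eligibility text side by side.**

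| Criterion | Study population/recruitment | Risks to the Subjects, A) | Elsewhere |
|---|---|---|---|
| HIV | excluded | not listed | – |
| Marijuana | excluded | not listed | Exclusion rule in Phase I, which controls skip; Table 1 screens at enrolment, V4 and V16 without saying whether controls follow it |
| No current EC use | not listed | stated for those willing to switch | Control rows of the Planned enrollment tables are labelled as having no e-cigs |

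The intent is probably the same for both groups, but no single place says so.

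**The case against.** Much can be said for the design. The run-in is deliberate: Expected Results explains that it spares likely relapsers a semi-invasive procedure and avoids the inflammatory phase that may follow cessation. The EC group is openly defined as smokers who successfully switch. Both groups share clinics, a minimum of 5 pack-years and, by intention, exclusion criteria. Controls may later re-enrol to try switching, so their unwillingness is not treated as permanent. Most importantly, the comparison is of changes, so stable differences in smoking history or dependence largely cancel. All of this stands, and it narrows the concern to differing trajectories and the post-switch baseline. It does not remove either.

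It can also be said that covariates belong in a statistical analysis plan. That holds for the detail of the model. The point here is the adjustment that the protocol does fix, which cannot do this job.

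Two stronger readings are tempting and not supported:

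- A reader might infer that controls who vape or use marijuana are admitted. The enrolment tables label controls as using no e-cigs, the exclusion list in Study population/recruitment is not limited to EC candidates, and Table 1 screens for marijuana at enrolment and V16. What remains is a drafting inconsistency. No rate of mixed exposure among controls can be put on it.
- A reader might size the bias by treating switchers as the top quarter of a normal trait and assuming a correlation with the endpoint. No such correlation is given. The calculation would also concern levels, not changes.

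**Conclusion.** The concern holds in limited form. The groups are selected by opposite criteria, with 75% to 85% of EC starters removed before the first NPD and no corresponding step for controls. Comparing changes protects against stable level differences, but not against different courses over the 12-week stability phase, and there is no pre-switch NPD. The stated adjustment cannot address the selection.

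The size and direction of any bias cannot be derived from the protocol. A reader might infer that ECs will look better than they are because lighter smokers switch. That rests on an assumption about who succeeds and how their measurements evolve, and the document supplies neither. That selection affects the endpoints at all is a plausible inference, not something the document shows.

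The exclusion-list mismatch is a separate and certain inconsistency of lesser weight. The point should be corrected, but it does not invalidate the study.

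**What to change.** 1. **Statistical Analysis paragraph.** Adjust the primary between-group comparison for smoking intensity before the switch: pack-years, and either enrolment plasma cotinine or enrolment COHb. For controls, use the first-visit sample. Keep the adjustment for on-study nicotine and puffs as secondary. With 50 subjects, limit this to one or two covariates. Residual degrees of freedom in a two-group comparison fall from 50 − 2 = 48 to 47 or 46.
2. **Eligibility.** Reconcile Study population/recruitment, Phase I and Smoker controls, Risks to the Subjects, A) and Table 1 into one list for both groups. State that the HIV, marijuana and no-current-EC criteria apply to controls, and that the Table 1 marijuana screen does too.
3. **Reporting.** Present the result as successful switchers against continuing smokers, and acknowledge residual confounding by motivation and ability to quit.

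The cost is protocol wording, the marijuana screen for controls if they do not already have it, and one or two degrees of freedom. Pack-years is already an entry criterion, and Table 1 already schedules enrolment plasma and COHb. It should be confirmed that controls have the corresponding first-visit values. No extra subjects are needed. Matching the 20 controls on several smoking variables is not proposed: cells would be sparse, and matching could not balance motivation or ability to quit.

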### C) Potential Risks

Collection of nasal lavage fluid and harvesting of nasal epithelial cells: this procedure carries minimal risks to the subject. It is sometimes associated with an unpleasant feeling due to the lavage, minimal risk of aspiration of part the 5 ml of sterile saline solution, and coughing. To prevent this from happening, the head of the patient will be bend forward during the collection, so the fluid will rinse out of the nose and not get into the pharynx where it can be swallowed or aspirated. Cell sampling with the microbrush can cause a mild discomfort and a mild nosebleed.

NPD measurement is a non-invasive method with minor risks, which includes swallowing and aspiration of the solution used for rinsing the nose. Even in case of accidental swallowing or aspiration, there are limited risks of a severe reaction, even in a respiratory impaired individual. Amiloride is a diuretic medication and can increase urine production when given in a higher dose, which is not expected here as the used dose is low and systemic absorption is not anticipated. Isoproterenol is a beta mimetic and can lead to tachycardia, hypertension and migraine. The dose used is low and the systemic absorption negligible. Other potential side effects include nosebleed, runny nose and coughing. For the study, a subcutaneous insertion of a butterfly needle is required, which brings a minimal risk of bruising, bleeding and infection. The butterfly is only used as a control electrode. No medications are injected through it into the skin or vascular system.

Collection of clinical information (demographics, adverse events): No significant physical risks arise from these procedures. There is always the risk of psychological distress and breach of confidentiality. In order to minimize this risk, written information is stored in locked files or file-rooms when not attended by study personnel. Data will be transformed to an electronic database using REDCap (registered under the University of Miami).

Blood draw: The risks from blood draw from a vein are minimal but include discomfort at the site of puncture, possible bruising around the puncture site, rarely an infection, and uncommonly, faintness from the procedure.

Pulmonary Function Testing is a routine clinical procedure with few risks. Patients are coached to make repeated forceful breathing efforts. The subjects might have chest soreness. Unusually, subjects may become lightheaded during these efforts. We will minimize this risk by having the PFT done in a sitting position.

EBC collection: may produce dizziness if the subject hyperventilates. We will minimize this risk by coaching subjects to keep a slow and paced respiration.

Electronic cigarettes: Known side effects of ECs include mouth/throat irritation (23), vertigo (23), headaches (23), bronchospasm (8, 24), and nausea (25) similar to those found with approved

nicotine replacement therapies (NRT). Other potential toxic effects are unknown and the goal of this proposal.

## **2. Adequacy of Protection Against Risks**

**A) Recruitment and Informed Consent:** Active smokers (N=140) will be recruited at the Miami VA Medical Center pulmonary function test laboratory as well as pulmonary and primary care clinics. IRB-approved advertisement and flyers will be used if necessary. We may also contact directly health care providers to refer active smokers.

Study candidates will be briefed about the study protocol and procedures and if interested will be invited to come on a separate day, where study investigators will explain the study objectives, process risks and benefits. Subjects will take the informed consent home and come on a follow-up day to sign and be enrolled. Subjects will have sufficient time to meet with the PI to address all their questions about the research.

**Informed consent:** The study protocols and their informed consent documents will be submitted for review to the Miami VA IRB. Subjects interested in volunteering for the study will have a lengthy discussion with the investigators about the risks and benefits of their participation.

### **B) Protection Against Risk:**

**General:** We will carefully select subjects that can tolerate the procedures of the study. Our Human Research Laboratories and Pulmonary Function Laboratory are fully equipped to handle possible fainting and other, more serious types of medical emergencies. A CPR cart will be available, as will adequate personnel (physicians trained in BLS and ACLS) to handle any potential emergency.

**Clinical and personal information:** All samples will be labeled with unique codes to protect the subject's identity. Samples will be catalogued using Freezerworks® software. There will be no way to match samples to subjects. All patient data will be stored in locked file cabinets or a room that is locked when unattended. All electronic data will be secured using password protection. Access to these data will be restricted to the research staff only. The study investigators will regularly monitor for safety issues.

**Electronic cigarettes:** At the present time there are no health warnings regarding the use of ECs based on objective data of their toxicity. The health warning is a word of caution due to the lack of these studies. Given that assessment of EC toxicity is the main goal of this proposal, subjects will be informed that risks are not well established and that they need to report any potential side effects immediately. It is possible that subjects may be allergic to components of the e-liquids (PG is more commonly mentioned in online blogs) with mild symptoms such as hoarseness and itchy throat. If any of these potential symptoms occur, subjects will have a complete clinical evaluation including additional lung function testing. The investigators will then consider withdrawal of the study depending on severity.

**NPD:** Having the patient bending the head forward will minimize the risk of aspiration of nasal irrigation solutions, by allowing the solution to drip out of the nose and not in the pharynx. The perfusion rate will be set at 0.5 ml/min for the nose to be rinsed with very low volumes.

**Pulmonary Function Testing:** Unusually, subjects may become lightheaded during these efforts. We will minimize this risk by having the PFT done in a sitting position.

## **3. Potential Benefits of the Proposed Research to the Subjects and Others**

[name] PI

ADVERSE AIRWAY EFFECTS OF INHALED NICOTINE FROM TOBACCO AND E-CIGARETTES

VERSION 3.3 09/28/2017

Subjects will not receive any direct benefit from participating in this project.

#### **4. Importance of the Knowledge to Be Gained**

The experiments to be done with the samples obtained from these subjects aim at understanding the potential toxicity of electronic cigarettes, devices of growing popularity that are currently unregulated. The knowledge gained may lead to potential new regulations about the use of these devices in the future.

#### **5. Data Safety and Monitoring Plan**

The study investigators will provide ongoing review of adverse event data. They will discuss adverse events with a committee formed by additional faculty members within the Pulmonary Division that can stop the study. Additional oversight will be provided by the IRB to whom adverse events and serious adverse events will be reported.

The study physicians and research coordinator will continually monitor the well being of all patients enrolled in the trial. The project members will meet monthly to review accruals to protocols, accrual goals, responses to protocol treatments, and serious adverse events. For individual side effects, study participation (and use of EC) will be discontinued. For group side effects, protocol modifications will be addressed accordingly and submitted to the IRB before they are implemented. Found toxicity will be reported to the FDA as well. No modifications to protocols are implemented until they are approved by the IRB. If changes are required to the consent form as a result of the serious adverse events, the consent is revised and submitted to the IRB for review and approval. All subjects are re-consented when the new information is being provided to and/or new risks are identified.

